#### 2.7.8. Perioperative Bleeding and Transfusion Requirements

Perioperative bleeding and transfusion requirements (liters) until discharge will be recorded.

#### 2.7.9. Readmission Rate for Any Reason

All-cause readmission within 30 days after surgery will be recorded and at all other assessment time points (8, 26 and 52 weeks postoperatively).

### 2.8. Statistical Analysis

#### 2.8.1. Sample Size Calculation

Power analysis for the sample size selection to highlight the preoperative program on the change in 3-day CAS was performed via the web application http://sampsize.sourceforge.net/ (accessed on 1 June 2021) for a significance level of α = 0.05 and power = 90%. The assumptions were made based on the study by Jérôme et al. [54], where m1 = 11.2 with a standard deviation = 3.1 and m2 = 13.6 with a standard deviation of 3.1. The minimal clinically important difference (MCID) between groups for the 3-day CAS was set at 2.4 units, given that the MCID for the 1-day CAS was found to be 0.8 units [39]. The ratio between groups will be 1:1. Due to factors such as in-hospital mortality, the drop-out rate is 10%. Considering the above assumptions, the minimum required sample to highlight the preoperative effectiveness of the exercise in the immediate postoperative basic mobility assessed with the 3-day CAS is set at 80 subjects (intervention group n1 = 40, control group n2 = 40).

The power analysis for sample size selection to demonstrate postoperative program change in the 6-minute walking test after program completion at eight weeks postoperatively was also performed via the web application: http://sampsize.sourceforge.net/ (accessed on 1 June 2021), with a significance level α = 0.05 and power = 90%. Based on previous studies [47,55,56], the 6MWT after a hip fracture at various time points (6 months, 20 days and one month postoperatively, respectively) varies approximately at 250 m of travel distance with a standard deviation of between 70 and 80 m. From the above-mentioned results, our assumptions for the power analysis, also assuming a clinically significant difference between the groups at 50 m, are m1 = 250 with a standard deviation = 75 and m2 = 300 with a standard deviation of 75. Considering the ratio between groups will be 1:1, the sample size is 96 patients (48 in each group).

However, based on the study by Karagiannis et al. [5] on a Greek population, mortality at six months after a fracture is 10.5%. However, both because this particular study reports a lower incidence of mortality at 6 and 12 months postoperatively compared to studies in other countries [57], and because of other factors that will likely contribute to the drop-out rate, such as comorbidities that will lead to the mandatory interruption of the program or the patient’s desire to interrupt the program for personal reasons, an increase in the sample size by 20% is deemed necessary, with the result that the sample size is set at 116 people (intervention group n1 = 58, control group n2 = 58).

Considering the above, in order to ensure the necessary power to investigate both primary purposes, the sample size is set at 116 subjects.

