#### 2.4.3. Withdrawal Criteria

Inability to participate in the inpatient program for more than two consecutive days (e.g., due to fever or early surgery within two days) or abstinence from more than 20% of the scheduled sessions in the postoperative programIntense subjective discomfort during exercise or development of other severe symptomatology or signs, as described in Section 2.4. Safety considerations and handling of adverse eventsPatient’s choice to drop out of the program

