There is less evidence about the value of prehabilitation, which is, however, suggested as appropriate, or even necessary, both for the prevention of postoperative complications and the best outcome of surgery [68,69], as well as for the favorable cost-effectiveness it offers [70]. Based on the existing literature on both the benefits of aerobic exercise on cardiorespiratory health and functionality in patients with hip fractures [17,64], the positive regulation it brings about in biochemical markers such as hypercoagulability [22,23] and albumin [71,72], we hypothesize that a pre- and postoperative exercise program can provide a comprehensive, multidimensional and multisystemic benefit to patients after a hip fracture. Delayed surgery, beyond 48 h of admission, is a worldwide issue [73]. Although, in regional hospitals, the length of waiting time might be considered during early surgery on average [74], in major hospitals, almost one-third are delayed surgeries in Greece [75]. Therefore, considering the Greek reality where, in hospital clinics, patients’ surgeries are delayed due to a disproportion in the number of cases and staff, resulting in a possible impact on patient outcomes [76], there is an immediate need to investigate the dynamics of such a conservative intervention in biochemical markers related to morbidity and mortality.

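### Early surgery is a named reason for withdrawal after randomisation, but neither drop-out allowance names it, so the stated 90% power for the two primary outcomes is not supported

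*Protocol article*

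**What the plan says.** Section 2.1 randomises patients 1:1 on admission to the emergency department, before the time to surgery is known. It sets recruitment at 116 and describes no replacement of withdrawn patients.

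Section 2.4.3 makes it a withdrawal criterion to be unable to take part in the inpatient program for more than two consecutive days. One of its two examples is "early surgery within two days".

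Section 2.8.1 has two calculations. For the 3-day CAS the assumptions are "where m1 = 11.2 with a standard deviation = 3.1 and m2 = 13.6 with a standard deviation of 3.1", and the allowance is "Due to factors such as in-hospital mortality, the drop-out rate is 10"%; the result is 80 patients. For the 8-week 6MWT the calculation is made "with a significance level α = 0.05 and power = 90"%, the assumptions "are m1 = 250 with a standard deviation = 75 and m2 = 300 with a standard deviation of 75", and the result before attrition is that "the sample size is 96 patients (48 in each group"). The text then cites 10.5% mortality at six months, adds comorbidities and personal wishes as further causes of loss, and concludes: "an increase in the sample size by 20% is deemed necessary, with the result that the sample size is set at 116 people". It states that 116 secures the power for both primary purposes.

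The Discussion treats surgery as delayed when it takes place more than 48 h after admission, and says that "in major hospitals, almost one-third are delayed surgeries in Greece".

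**The concern.** Early surgery happens after randomisation, and in this population it is an ordinary event. If almost one-third of operations are delayed beyond 48 h, most are not, and those patients fall in or near the window that section 2.4.3 gives as an example of a reason for withdrawal. The two allowances are explained by death, comorbidity and patient choice. A cause of loss that could be larger than all of these together is named in one section and left out of the sizing in another.

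Both primary power statements are at stake. The CAS comparison is the more exposed of the two, because it tests the preoperative program, and patients operated on early receive little of that program whether or not they stay in the analysis. If they were also removed from the analysis, the result would describe only patients who waited longer, a narrower group than the eligibility criteria define.

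**Working it through.** **Inputs (section 2.8.1).** 6MWT: difference 300 − 250 = 50 m, SD 75 m. CAS: difference 13.6 − 11.2 = 2.4 points, SD 3.1. Alpha 0.05, power 90%. Sidedness is not stated; two-sided reproduces the plan's 6MWT figure (one-sided would give 39 per arm).

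**Reproducing the plan.** n per arm = 2 × (1.960 + 1.282)² × (SD/difference)², where (1.960 + 1.282)² = 10.507.
- 6MWT: 2 × 10.507 × (75/50)² = 47.3, so 48 per arm and 96 in total. Matches.
- CAS: 2 × 10.507 × (3.1/2.4)² = 35.1, so 36 per arm; 36/0.90 = 40 per arm and 80 in total. Matches.
- Inflation: 96 × 1.20 = 115.2, so 116. Matches.

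**How much loss 116 absorbs.**
- 6MWT: 1 − 96/116 = 17.2%. To keep 96 after a 20% loss, 96/0.80 = 120 are needed.
- CAS: 1 − 36/58 = 37.9%.
- If the cited 10.5% mortality is taken as loss, 116 × 0.895 = 103.8 remain. Then only 1 − 96/103.8 = 7.5% of those could be lost for any other reason before the 6MWT margin is used up.

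**Case A: withdrawn patients leave the analysis.** Two-sided t-test power (noncentral t) for the number left per arm out of 58. The loss shares are assumptions.

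| Loss | Per arm | 6MWT | CAS |
|---|---|---|---|
| 20% | 46 | 88.6% | 95.7% |
| one-third | 39 | 83% | 92% |
| one-half | 29 | 70% | 83% |
| two-thirds | 19 | 52% | 64% |

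For comparison, the t-test gives 89.8% at the planned 48 per arm (6MWT) and 90.0% at 36 per arm (CAS). The normal formula used for sizing gives 90.4% at 48.

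**Case B: they are kept and analysed as randomised.** Sample size is preserved, but the CAS difference is averaged over patients with and without a full preoperative program. Take 58 × 0.90 = 52 per arm after the plan's 10% loss, and assume that two-thirds have early surgery.
- They get half the effect: (1/3) × 2.4 + (2/3) × 1.2 = 1.6 points; power about 74%.
- They get no effect: (1/3) × 2.4 = 0.8 points; power about 26%.

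For 6MWT, Case B stays near 90% if these patients complete the postoperative phase, are measured at eight weeks, and total loss from all causes stays at or below about 17%.

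**The case against.** The strongest objection is that nothing in the article shows two-thirds of patients being lost. A reader might infer this by taking the complement of the Discussion's figure, and conclude that power will be 52% and 64%. The documents do not support that. The one-third figure describes major Greek hospitals in general and comes from a cited source; it is not this site's rate. The Discussion presents surgical delay as a reason for doing the trial, and the Figure 1 legend says the time to surgery will vary. The operative test in section 2.4.3 is being unable to take part for more than two days, with early surgery only an example, and how surgery within two days meets that test is unclear. Nor does the article say that withdrawn patients go unmeasured or leave the analysis; one criterion speaks of dropping out of the program. For the same reason, it does not follow that the result would apply only to patients with delayed surgery. All of this stands, and it is why the losses above are shown as a range of assumptions.

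It is also fair that the causes listed in section 2.8.1 are introduced as examples, so early surgery is unnamed but not expressly excluded. Against that, the 6MWT allowance is nearly used up once the cited mortality is counted as loss.

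The difference between 20% and 17% could be defended too: the text says the sample is increased by 20%, which it is. At 20% loss the shortfall is about one point of power. This is a wording correction and does not carry the concern.

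What survives is a conflict between sections that the article itself fixes, so a later analysis plan would not remove it.

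**Conclusion.** The concern holds in this form: the withdrawal criterion, the attrition allowances and the Discussion's statement on surgical delay do not fit together, and the 90% power claimed for both primary purposes is therefore not supported.

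The size depends on two things the article does not give: the site's early-surgery rate, and whether withdrawn patients are analysed. If they are excluded, 6MWT falls below 90% once total loss passes about 17%, and CAS once it passes about 38%. Two-thirds lost is the unfavourable end of the range examined, not a forecast. If they are retained, 6MWT can be protected, but CAS power depends on how much effect a shortened preoperative program has. The 74% and 26% figures both assume two-thirds early surgery and differ only in that effect. All figures take the plan's means and SDs as stated, with two-sided testing.

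**What to change.** 1. Reconcile sections 2.4.3 and 2.8.1 and the Discussion. Say what the early-surgery example means beside the more-than-two-days test, and whether withdrawal means leaving the program or leaving the study. How these patients are treated is the sponsor's decision.
2. State that patients who meet the early-surgery criterion are still assessed for 3-day CAS and 8-week 6MWT and are analysed as randomised. If only patients with longer waits are the target population, define that before allocation instead.
3. Restate power for both outcomes over an explicit range of early-surgery rates, using the site's own rate if available. For CAS, include a range for the effect in patients who receive few preoperative sessions.
4. Replace the 20% sentence: 116 allows for about 17% loss on 6MWT, and at 20% loss its power is about 89%.

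**Cost.** Items 1, 3 and 4 are wording and recalculation. Item 2 means following up patients who might otherwise be dropped. The real downside is that the restated CAS power will be lower because of dilution, possibly well below 90%. With no effect in early-surgery patients it can even fall below the figure obtained by excluding them (26% against 64% when two-thirds are operated on early). The sponsor would then have to decide whether 116 is still enough for the CAS purpose.

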## 3. Discussion

This study has two primary purposes. First, to study the effect of a preoperative aerobic exercise program with a portable upper extremity cycle ergometer on immediate postoperative mobility. Second, to investigate the additional effect of an 8-week postoperative aerobic exercise program with a portable upper extremity cycle ergometer on the walking distance at 8 weeks after surgery. This study also has a number of secondary objectives. Regarding the preoperative exercise program evaluation of the effect of the preoperative program on surgical stress (via blood lactate levels), perioperative bleeding and transfusion requirements, hemostasis factors will be evaluated, in addition to, an evaluation of the effect of the postoperative program in the short and long term: lower extremity functionality, aerobic capacity, nutritional status, hemostasis factors, mortality, rehospitalization and complications related to surgery and hospitalization (thrombotic and thromboembolic events).

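### Two primary outcomes are each sized at the full two-sided 0.05 with no rule linking them, so if either may be claimed the chance of a false primary claim is about 9–10%

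*Protocol article*

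**What the plan says.** The Discussion (section 3) states: "This study has two primary purposes". The first is the effect of the preoperative programme on immediate postoperative mobility, and the second the additional effect of the postoperative programme on walking distance at 8 weeks. Table 1 marks CAS and 6MWT in bold as the primary outcome measures.

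Section 2.8.1 has a separate power analysis for each:

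- **3-day CAS:** "for a significance level of α = 0.05 and power = 90" per cent, with "m1 = 11.2 with a standard deviation = 3.1 and m2 = 13.6 with a standard deviation of 3.1". Losses: "Due to factors such as in-hospital mortality, the drop-out rate is 10" per cent. Result: 80 patients, 40 per arm.
- **8-week 6MWT:** "with a significance level α = 0.05 and power = 90" per cent, with "m1 = 250 with a standard deviation = 75 and m2 = 300 with a standard deviation of 75". Result: 96 patients, 48 per arm. For losses, "an increase in the sample size by 20% is deemed necessary", which gives 116 patients, 58 per arm.

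The section closes by choosing the larger figure for both: "in order to ensure the necessary power to investigate both primary purposes, the sample size is set at 116 subjects".

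There is one 1:1 randomisation, at admission (2.1). The intervention arm receives both exercise programmes. The control arm receives attention activities before surgery and no study intervention after it (2.1, 2.5). Section 2.8.2 gives a t-test or Mann–Whitney comparison of the two groups. It states no significance level and no rule that connects the two primary tests.

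**The concern.** Both primary comparisons use the same randomised contrast in the same patients, and the sizing gives each the whole 5%. Nothing says whether one success is enough, whether both are needed, or whether one test comes first. As it stands, a report could present whichever outcome reached p < 0.05 as a primary effect. The 5% level would then describe each test but not the set of primary claims, and the trial would have roughly twice the nominal chance of a false one. A linking rule carries weight only if it is written down before results are seen.

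**Working it through.** **1. Reproduce the plan's sizes.** Normal approximation, 1:1 allocation: n per arm = 2(z₁₋α/₂ + z₀.₉₀)² × (SD/difference)².

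With two-sided α = 0.05, 2(1.960 + 1.282)² = 21.01.

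- CAS: 21.01 × (3.1/2.4)² = 35.1, so 36 per arm; 36/0.90 = 40 per arm, 80 in total. This matches.
- 6MWT: 21.01 × (75/50)² = 47.3, so 48 per arm, 96 in total; 96 × 1.20 = 115.2, so 116. This matches.

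The protocol does not state sidedness, so the alternatives were tried:

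- One-sided 0.05 gives 29 and 39 per arm before losses, which does not match.
- Two-sided 0.025 each (a halved alpha) gives 42 and 56, which does not match.

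The sizes therefore rest on the full two-sided 0.05, used twice.

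**2. Chance of at least one false primary result when the programme affects neither outcome.**

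If independent: 1 − 0.95² = 0.0975. For correlated test statistics, the value is 1 − P(|Z₁| < 1.96 and |Z₂| < 1.96) under a bivariate normal. The documents give no correlation, so a range is assumed. Under Holm (smaller p against 0.025, then the other against 0.05) the independent value is 1 − 0.975² = 0.0494.

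| Assumed correlation | Both at 0.05 | Holm |
|---|---|---|
| 0 | 9.75% | 4.94% |
| 0.3 | 9.5% | 4.8% |
| 0.5 | 9.1% | 4.6% |

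**3. Power under Holm.**

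The expected test statistic is (difference/SD) × √(n/2). Evaluable numbers per arm:

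- CAS: 58 × 0.90 = 52.
- 6MWT: the required 48 (58/1.20 = 48.3).
- Harsher case: a true 20% loss, 58 × 0.80 = 46 for both.

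At 52 and 48 the expected statistics are 0.774 × √26 = 3.95 (CAS) and 0.667 × √24 = 3.27 (6MWT). Single-test power is 97.7% and 90.4% at 0.05, and 95.6% and 84.7% at 0.025.

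With independent tests, Holm power for 6MWT is its power at 0.025 plus the gain from 0.025 to 0.05 when CAS has passed 0.025: 0.847 + (0.904 − 0.847) × 0.956 = 0.902. Correlated cases use the same rule with bivariate normal probabilities.

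| Scenario | 6MWT, no rule | 6MWT, Holm | CAS, no rule | CAS, Holm |
|---|---|---|---|---|
| Both effects real, 52/48 per arm | 90.4% | 90.2% to 89.9% | 97.7% | 97.3% to 96.7% |
| Both effects real, 46/46 per arm | 89.2% | 88.8% to 88.3% | 96.0% | 95.5% to 94.7% |
| Only 6MWT real, 48 per arm | 90.4% | 84.9% | – | – |
| Only CAS real, 52 per arm | – | – | 97.7% | 95.7% |

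Ranges run from correlation 0 to 0.5.

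**4. Dependence on the CAS inputs.** Section 2.7.1 gives the 3-day CAS a maximum of 9, yet 2.8.1 assumes means of 11.2 and 13.6. (The item scoring in 2.7.1, three items of 0–2 over three days, gives 3 × 2 × 3 = 18.) The error rates in step 2 do not use these means, but the CAS power does. Because Holm links the tests, 6MWT power depends on it too. If CAS power at 0.05 were only 80%, 6MWT power under Holm at 48 per arm would be 88.8% to 87.5%. At 50% it would be 86.9% to 85.6%.

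**The case against.** **The rule may sit elsewhere.** This is a condensed article, an analysis plan may exist, and a multiplicity rule is often placed there. A reader might infer that the protocol orders both outcomes to be tested at 0.05. It does not: the 0.05 figures stand in the sample-size section, and 2.8.2 names no level. What remains is that the article fixes the full alpha for each primary and bases 116 on it. Any linking rule kept elsewhere would still require the power statement to be redone.

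**These may be two claims, not one.** CAS on days 1–3 reflects almost only the preoperative programme, since a three-times-weekly postoperative programme has barely begun. 6MWT at 8 weeks reflects the whole package. Whether distinct claims need joint control is disputed. That is fair, but the protocol does not make the argument. There is also no second randomisation at surgery, so both outcomes test the same arms.

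**No success criterion is stated.** A reader might infer that either outcome alone counts as trial success. No passage says so, nor does any require both. The 9–10% figure is therefore conditional on either being claimable.

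**Holm is not free.** A reader might infer that adjustment costs almost nothing. That holds only if both planned effects are real and losses stay as planned. The cost to 6MWT is about 5.5 points if CAS shows no true effect.

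**Holm is one choice among several.** A fixed sequence or a both-must-succeed rule would also control the error. This stands.

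**Conclusion.** The point holds in conditional form. The protocol sizes two primary outcomes on one randomised contrast at the full two-sided 0.05 each and links them by no rule. If either may be claimed, the chance of at least one false primary claim under no effect is 9.75% with independent tests and 9.1% at an assumed correlation of 0.5. The exact value depends on a correlation that the documents do not give.

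Table 1 bolds whole rows, including CAS at 4 weeks and 6MWT at 4, 26 and 52 weeks. A reader might infer that these are primary tests too and that the error is larger still. The stated purposes and the sample-size section name only the 3-day CAS and the 8-week 6MWT, so that reading is not adopted.

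This does not make the trial unsound. It leaves the status of a single positive primary result undefined, and that should be settled before results are known.

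**What to change.** State in 2.8 that the two primary tests are controlled at an overall two-sided 5%. One suitable wording is Holm: the smaller p-value is compared with 0.025 and, if it passes, the other with 0.05. A fixed sequence or a both-must-succeed rule would also serve, if chosen in advance. Restate the power of each outcome under the chosen rule.

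The cost is a sentence and a revised power statement, with 116 unchanged. Under Holm the restatement should disclose three things:

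- With both planned effects real, the loss is about 0.2–0.9 points at 52 and 48 evaluable per arm. It reaches up to about 1.3 points at 46 per arm, where 6MWT power is about 88–89%, just under the 90% target.
- If only the 6MWT effect is real, its power is about 84.9%.
- The CAS power is provisional until the assumed means in 2.8.1 and the scale range in 2.7.1 are reconciled.

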#### 2.8.2. Data Analysis

Descriptive statistics will be used to summarize the baseline characteristics of the patients participating in each group. Continuous variables will be presented with the mean and standard deviation or median and interquartile ranges (IQR) if they do not follow a normal distribution. Categorical variables will be presented with absolute and relative frequencies (n, %). The Kolmogorov–Smirnov test will be performed to check for normality. Based on the normal or non-normal distribution of the sample, a *t*-test or Mann–Whitney test will be performed to compare the means or medians of the two groups, respectively. The chi-square test will be used to identify differences in the categorical variables between the two groups. A subgroup analysis will be performed a posteriori for the different surgical techniques used for all variables.

To detect confounding factors that may affect the functional tests (CAS, 6WMT and TUG), multiple linear regression will be performed after first performing the relevant check on whether the conditions are met to consider the linear regression results reliable. If the necessary conditions are not met, the necessary transformations of the dependent variables will be carried out.

To test the change of the parameters to be measured at multiple time points (e.g., albumin, functional score, etc.) and to compare the change between the intervention group and the control group, we will perform an analysis of variance for repeated measurements (repeated measures ANOVA).

Additionally, the time to occurrence of an event (e.g., death, readmission to hospital, thrombosis, etc.) will be presented with a Kaplan–Meier survival curve. To highlight the factors related to the time of occurrence of an event, semiparametric (Cox proportional hazard models) or parametric survival analysis models (e.g., Weibull, exponential, etc.) will be performed, as will result from the analysis that will be done.

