### 2.7. Outcome Measures

For all scales and questionnaires, permission to use has been granted after personal communication with the creators or with the team that has carried out the validation in the Greek population. All outcome measure measurements will be performed by an examiner blinded to the allocation group of the assessed (single-blinded). The demographic characteristics, fracture type, surgical technique and pre-fracture level of independence will be collected. All measurements will be performed in a lab setting.

The pre-fracture level of independence will be evaluated using the New Mobility Score (NMS). The NMS consists of three questions assessing the ability to walk in daily activities. The NMS is completed by the patient or by the caregiver in cases of cognitive impairment. The patient is asked to answer for pre-fracture walking ability the following: (1) able to move around the house (indoor walking), (2) able to go outside the house (outdoor walking) and (3) able to go shopping (walking while shopping). Each question can be scored from 0 to 3 points based on the patient’s self-reported ability, where 0 points correspond to an inability to perform, 1 point to assistance from another person, 2 points to use of an aid and 3 points to independent performance without assistance. The total score ranges from 0 to 9 points, with a score of 6 points or less indicating low functional capacity, while more than 6 points reflects a high level of pre-fracture function in patients with hip fractures. A score equal to or greater than 7 points justifies the rapid release of the patient from the hospital without the need for further in-hospital rehabilitation after surgery [38,39].

Table 1 represents the scheduled timeline of all the outcome measures.

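### A normality pre-test decides whether the primary outcomes are compared as means or by ranks, and no adjusted mean-difference analysis is fixed although the trial was sized on mean differences

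*Protocol article*

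**What the plan says.** Section 2.8.2 (Data Analysis) states that "The Kolmogorov–Smirnov test will be performed to check for normality". Depending on that result, the two groups are compared by a t-test on means or by a Mann–Whitney test, which the text describes as a comparison of medians.

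The same section adds two further analyses that reach the primary outcomes:

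- A regression: "To detect confounding factors that may affect the functional tests (CAS, 6WMT and TUG), multiple linear regression will be performed". The outcome is to be transformed if the model conditions fail.
- Repeated-measures ANOVA for parameters measured at several times. The 6MWT is measured at weeks 4, 8, 26 and 52.

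No analysis is identified as the treatment comparison for 3-day CAS or for week-8 6MWT.

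Section 2.8.1 (Sample Size Calculation) works entirely in means. For CAS it assumes values "where m1 = 11.2 with a standard deviation = 3.1 and m2 = 13.6 with a standard deviation of 3.1", and the difference "between groups for the 3-day CAS was set at 2.4 units". For 6MWT it assumes 250 m against 300 m with SD 75.

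On baseline data, section 2.7 says "The pre-fracture level of independence will be evaluated using the New Mobility Score (NMS"). It also collects demographic characteristics and fracture type.

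**The concern.** A trial sized to detect 2.4 points or 50 m should report a difference in points or metres. If the gate switches to Mann–Whitney, the test addresses whether values in one group tend to exceed those in the other. That is not a mean difference, and in general it is not a difference in medians either. The reader cannot know beforehand which quantity the primary result will describe.

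The planned regression does not settle this. It is framed as a search for confounders, although randomisation removes systematic baseline confounding. The useful role of baseline covariates in a randomised comparison is to reduce residual variance in the treatment contrast. NMS, age and fracture type are known at admission, but the t-test and Mann–Whitney test do not use them.

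**Working it through.** **1. The plan's own sample sizes.** Two-sided α = 0.05 and power 90% (the text says "for a significance level of α = 0.05 and power = 90" per cent; sidedness is not stated). Formula per arm: n = 2(1.960 + 1.282)² × (SD/Δ)² = 21.01 × (SD/Δ)².

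- CAS: 21.01 × (3.1/2.4)² = 35.1, so 36. With 10% dropout, 36/0.9 = 40 per arm. The plan "is set at 80 subjects (intervention group n1 = 40, control group n2 = 40"). Reproduced.
- 6MWT: 21.01 × (75/50)² = 47.3, so 48 per arm and 96 in total. Raised by 20%: 96 × 1.2 = 115.2, so 116. Reproduced.
- One-sided testing gives 29 and 39 per arm and does not reproduce.

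The design is therefore an unadjusted, two-sided comparison of means.

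**2. How often the gate switches the test.** Each arm was tested at 5% in 2,000 simulated trials per scenario. CAS was rounded to integers on an assumed 0–18 range (three items scored 0–2 over three days). That range is an assumption: section 2.7.1 gives a maximum of 9, which the planning means of 11.2 and 13.6 exceed.

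| Scenario | Plain KS, mean and SD estimated | Lilliefors version |
|---|---|---|
| 6MWT normal, 48 per arm | 0.1% | 9.7% |
| 6MWT mildly skewed, 48 per arm | 0.7% | 28.9% |
| CAS, 36 per arm | 0.9% | 46.4% |
| CAS, 52 per arm (58 less 10%) | 1.8% | 67.1% |

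Entries are the share of trials in which at least one arm rejects. Treating the two arms as alike, the last row means 1 − √(1 − 0.671) = 43% per arm with Lilliefors and 1 − √(1 − 0.018) = 0.9% with plain KS. The article does not say which version is meant.

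**3. What the gate costs.**

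- With no true effect, the two-stage rule rejected in 5.0% of trials for both 6MWT and CAS.
- With the planned effect, its power was 88.8–89.8% for 6MWT (t-test 88.8–89.8%), and 89.4–89.6% for CAS at 36 per arm (t-test 89.4%).
- The t-test and Mann–Whitney disagreed on significance in about 1–4% of trials.

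**4. What adjustment would gain.** Residual SD = SD × √(1 − r²), where r is the correlation of the covariate with the outcome. Equivalent increase in patients = 1/(1 − r²) − 1. The documents give no r, so 0.3 to 0.5 is assumed. Power is for 6MWT at 48 per arm from the noncentral t distribution, with d = 50/75 = 0.667 unadjusted.

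| r | Residual SD (m) | Power | Equivalent extra patients |
|---|---|---|---|
| 0 | 75.0 | 89.8% | – |
| 0.3 | 71.5 | 92.3% | 10% |
| 0.4 | 68.7 | 94.1% | 19% |
| 0.5 | 65.0 | 96.2% | 33% |

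If a full 20% is lost (58 × 0.8 = 46 per arm), the large-sample formula gives 89.2% unadjusted and 91.8%, 93.7% and 95.8% for the same three values of r.

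**The case against.** The t-test/Mann–Whitney rule is generic wording, and the article never labels it the primary analysis. A regression on CAS and 6MWT is planned, and with treatment group and baseline covariates it would be the adjusted analysis asked for. A condensed article may leave the covariate list to a fuller document. The unadjusted design already has about 90% power at its own evaluable numbers. CAS is described as ordinal, so a rank test is defensible. If some patients score 0 m, ranks can be stronger: with 8% zeros per arm, a 50 m shift and SD 75, one simulation gave Mann–Whitney 75.5% power and the t-test 58%.

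Much of this stands. The missing covariate list is not a fault in itself, and adjustment is a gain on offer rather than the repair of an underpowered design. The regression, however, is written as a search for confounders with outcome-dependent transformation, not as the treatment contrast. The case for ranks is a case for fixing the test in advance: in that zeros scenario the two tests disagreed in 19% of runs.

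Three stronger readings are tempting and are not supported:

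- A reader might infer that the pre-test inflates type I error or wastes power. The simulations show neither.
- A reader might infer that the primary outcomes receive no adjusted analysis at all. The planned regression contradicts that.
- A reader might add that two primary tests at 0.05 give a 9.75% chance of a false claim (1 − 0.95²). That figure assumes independent tests, whereas the same patients supply both outcomes and the article poses two distinct questions. It does not carry this point.

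**Conclusion.** The point holds in a limited form. Section 2.8.2 lets the trial's own data choose between a mean comparison and a rank comparison, misdescribes the latter as a test of medians, and leaves regression and repeated-measures ANOVA competing for the same outcomes. This does not match a sample size built on mean differences. How often the choice switches depends on the unstated KS variant, from about 2% to about 67% of trials for CAS at 52 per arm under the assumed 0–18 integer scale.

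The harm is an estimand that is not fixed and precision that is not used. The gain from adjustment, 2 to 6 percentage points of power for 6MWT at 48 per arm, is certain in direction only if the covariates predict the outcome, and its size rests on the assumed correlation of 0.3–0.5. This is a free improvement, not a flaw that invalidates the design.

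**What to change.** Remove the normality gate for the primary outcomes. Name one primary analysis for 3-day CAS and one for week-8 6MWT: a linear model of the mean difference between groups, adjusted for pre-fracture NMS, age and fracture type, with robust or bootstrap confidence intervals, reported in points and metres. Keep Mann–Whitney as a sensitivity analysis and describe it as a rank comparison. State that the confounder-search regression and the repeated-measures ANOVA are supportive, and drop data-driven transformation of the primary outcomes.

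The cost is analysis wording, settled before outcome data are seen. No new data, visits or patients are needed, since all three covariates are known at admission. The adjusted model uses a few degrees of freedom, which is negligible at this size. Whether to add a testing order for the two primary outcomes is a separate, optional choice: a fixed order would make the second outcome exploratory if the first fails.
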